#### **7.2.4.5 Craving scores**

Opioid craving scores are measured at Day 7 by a visual analog scale. The variable of interest is CRV.CROPIDSR and has possible values from 0 (definitely do not desire opioids) to 100 (definitely do desire opioids).

#### **7.2.4.6 Satisfaction questionnaires**

Satisfaction is measured at Day 7 on the Patient Satisfaction XR-BUP Questionnaire and the Patient Satisfaction & Adherence SL-BUP Questionnaire. Overall experience with XR-BUP (S99.S9MDEVAL) and SL-BUP (A99.A9SLEXP) is rated on a scale from 1 (completely ineffective) to 5 (completely effective). Importance of various reasons pertaining to medication use is rated on a scale from 1 (not important) to 7 (extremely important).

#### **7.2.4.7 Overdose events**

Overdoses in the past 30 days post enrollment will be captured by participant self-report and review of medical records. Data is captured on the ODE form.

### **7.2.5 Analyses of Secondary Outcome Measures**

#### **7.2.5.1 Engagement in MOUD at 7 days**

This variable will be analyzed as described in Section 7.2.2 for the primary outcome.

#### **7.2.5.2 Engagement in formal addiction treatment at 30 days**

This variable will be analyzed as described in Section 7.2.2 for the primary outcome.

#### **7.2.5.3 Engagement in MOUD at 30 days**

This variable will be analyzed as described in Section 7.2.2 for the primary outcome.

#### **7.2.5.4 Self-reported days of illicit opioid use**

Counts of self-reported illicit opioid use will be compared between treatment groups at both 7 and 30 days using negative binomial regression. These models will include treatment and covariates for outcomes measured at baseline as well as site, age, sex, ethnicity, race, treatment seeking, and insurance status (see **Exhibit 2**). Linear contrasts will be used to estimate treatment differences along with 95% confidence intervals for XR vs. SL at each follow-up time.

| Exhibit 2: Covariates for Primary and Secondary Outcomes |                        |                           |                                                                  |
|-----------------------------------------------------------------|------------------------|---------------------------|------------------------------------------------------------------|
| Covariate                                                | Variable name   | Coding in analysis | Comments                                                  |
| Treatment                                                       | COREVARS.TRT           | categorical               | XR-BUP, SL-BUP                                                   |
| Visit                                                           | VISNO                  | categorical               | Day 7, Day 30                                                    |
| Site                                                            | DEM.SITE               | categorical               |                                                                  |
| Age                                                             | DEM.DEBRTHDT           | continuous                | Age at randomization                                             |
| Sex                                                             | DEM.DESEX              | categorical               | Male, Female                                                     |
| Ethnicity                                                       | DEM.DEHISPNC           | categorical               | Hispanic, Non-Hispanic, Unknown/not reported                     |
| Race                                                            | DEM.WHITE, DEM.DEBLACK | categorical               | Black, White, Other, Unknown/not reported                        |
| Engagement in prior 12 months                                   |                        | categorical               | Engaged, not-engaged                                             |
| Treatment seeking at the index ED visit                         | EDR.ERPRBTYP           | categorical               | Yes ('Seeking referral for OUD treatment'), no (other responses) |
| Insurance status used for randomization                         | ER0099RC.E99RINSR      | categorical               | No insurance, public insurance, private insurance                |

Note: Unless noted otherwise, covariate values will be missing if the underlying variable(s) are missing.

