## 12.6 Statistical Methods

### 12.6.1 General Approach

Nominal and ordinal categorical variables will be summarized using frequencies and percentages. Continuous variables will be summarized with the following descriptive statistics: N, mean, standard deviation, median, minimum, maximum, interquartile range, and range.

No imputation of missing data will be performed in the primary and secondary analyses. Diagnostic tests and sensitivity analyses will be performed. For evaluation of effectiveness, all analyses will follow the intention to treat principle including all patients in their randomized group regardless of treatment received.

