#### **3.2.1.1 Intent-to-Treat (ITT) Population**

The ITT population consists of all ED participants who provided informed consent and were randomized into the study. ITT analyses will be performed according to the participant's randomized treatment arm.

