(MCAR). Robins, Rotnitzky and Zhao proposed an extension of GEE called the weighted GEE to alleviate this restrictive assumption. The weighted GEE provides consistent parameter estimates when the dropout mechanism is correctly classified by implementing the inverse-probability weighted method to account for dropouts under the missing at random (MAR) assumption. Inverse probability weights are estimated by a logistic regression of dropout at a particular measurement occasion. The dropout model will include baseline demographic and clinical characteristics including treatment engagement prior to enrollment, site, treatment group, insurance status and time as well as outcomes at previous timepoints. From the dropout model, predicted probabilities of dropout will be estimated for each subject at each post-randomization timepoint. The predicted probabilities will then be translated into weights where the weight is the inverse of the cumulative probability of dropping out at a particular assessment. Prior to final analysis, weights will be evaluated for outliers ( $>3$ ). If identified, additional covariates in the logistic model and/or trimming of weights will be considered to correct for this. The weighted GEE model will contain an effect for intervention (XR vs. SL). An exchangeable working correlation will be used to account for clustering responses from the same participants (i.e., 7 and 30 days). The model will also include treatment engagement in prior 12 months from baseline, age, sex, ethnicity/race, insurance status and site (see **Exhibit 2** below). Linear contrasts will be used to estimate odds ratios, treatment differences and 95% confidence intervals for the proportions of participants that engage in treatment in XR vs. SL at both 7- and 30-days follow-up.

The following SAS System code will be used for the GEE analyses. The variables in the models are as follows:

- *primdat*: primary outcome analysis file,
- *patid*: patient ID,
- *site*: site ID,
- *site2*: site ID with small sites ( $\leq 20$  randomized) pooled into one site,
- *treat*: treatment arm - XR-BUP or SL-BUP,
- *engage*: engagement variable where 1 = engaged and 0 = not engaged,
- *exist*: 1 if *engage* is not missing and 0 if *engage* is missing,
- *visit*: study visit (Day 7 or Day 30),
- *gender*: categorical variable for gender,
- *race\_cat*: categorical variable for White, Black, Other race, unknown or not reported,

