- *ethnic\_cat*: ethnicity category for Hispanic, not Hispanic, unknown or not reported,
- *insurance\_rand*: categorical variable for insurance status used for randomization - private, public, or no insurance,
- *prior\_engagement*: ?

1. Compute the weights for Day 7. The weights will be  $1/\text{pred07}$  where *pred07* is the probability that the outcome variable is not missing.

```
proc logistic data = primdat;
  class exist site site2 (ref = '02156') patid trt (ref = 'SL-BUP')
    gender (ref = '1') race_cat (ref = '1') ethnic_cat (ref = '0')
    insurance_rand (ref = '1') / param = ref;
  model exist (desc) = trt site2 age gender race_cat ethnic_cat
    insurance_rand /*prior_engagement*/;
  output out = denom07 predicted = pred07;
  where visno = 'C07';
run;
```

2. Compute the weights for Day 30. The weights at Day 30 are cumulative and will be computed as  $(1/\text{pred07}) * (1/\text{pred30})$ .

```
proc logistic data = primdat;
  class exist site site2 (ref = '02156') patid trt (ref = 'SL-BUP')
    gender (ref = '1') race_cat (ref = '1') ethnic_cat (ref = '0')
    insurance_rand (ref = '1') engage07 / param = ref;
  model exist (desc) = trt site2 age gender race_cat ethnic_cat
    insurance_rand /*prior_engagement*/ engage07;
  output out = denom30 predicted = pred30;
  where visno = 'C30';
run;
```

3. Run the final model with the computed weights. Treatment effects will be assessed at each visit using the *diffs* output from the *lsmeans* statement.

```
proc genmod data = final;
  class engage site site2 (ref = '02156') patid trt (ref = 'SL-BUP')
    visno (ref = 'C07') gender (ref = '1') race_cat (ref = '1')
    ethnic_cat (ref = '0') insurance_rand (ref = '1');
  model engage (desc) = trt visno trt * visno site2 age gender race_cat
    ethnic_cat insurance_rand /*prior_engagement*/ /
    dist = bin link = logit;
  weight wgt;
  repeated subject = patid / corr = cs;
  lsmeans trt * visno / pdiff oddsratio cl;
  output lsmeans = lsmeans diffs = diffs;
run;
```

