#### **7.2.7 Missing Data**

Several strategies were imposed to accommodate the likelihood that missing data will occur during this study including prevention, strict data collection procedures, careful selection of variables without large proportions of missing values, and regular monitoring of the trial. Despite these prevention efforts it is reasonable to assume missing data will occur. Our proposed primary and secondary analyses make use of all available data and are valid under the assumption that missing data will be missing at random (MAR) (Diggle, et al., Molenberghs, et al.). We may evaluate the plausibility of this assumption by determining the extent of missing data and use logistic regression to identify factors associated with missing data. We may conduct sensitivity analysis using a pattern-mixture approach implemented using multiple imputation under missing not at random (MNAR) assumptions to examine the robustness of conclusions of the primary analysis to missing data (Little, et al., Molenberghs, et al.).

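### A randomised participant with an observed outcome but a missing baseline covariate drops out of the ITT models; the exposure is narrow and the likely cost small

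*Combined protocol and SAP*

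**What the plan says.** **Who is to be analysed.** SAP 3.2.1.1: "The ITT population consists of all ED participants who provided informed consent and were randomized into the study". Protocol 12.6.1: "all analyses will follow the intention to treat principle including all patients in their randomized group regardless of treatment received". SAP 7.2.7 adds a statement that ends by invoking the MAR assumption: "Our proposed primary and secondary analyses make use of all available data and are valid under the assumption that missing data will be missing at" (quote cut short here).

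**Covariates in the primary model.** SAP 7.2.2: "The model will also include treatment engagement in prior 12 months from baseline, age, sex, ethnicity/race, insurance status and site". Exhibit 2 codes race and ethnicity with a level for unknown or unreported values. Sex has two levels (male, female) and prior engagement has two (engaged, not engaged), with no level for unknown. Treatment seeking is yes, or no for any other response.

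**What happens to a missing value.** The note under Exhibit 2: "Unless noted otherwise, covariate values will be missing if the underlying variable(s) are missing". Protocol 12.6.1: "No imputation of missing data will be performed in the primary and secondary analyses".

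**The code.** In SAP 7.2.2 the Day 7 logistic step saves its prediction with "output out = denom07 predicted = pred07". The SAP explains that this quantity "is the probability that the outcome variable is not missing", and its inverse is the weight. The two weight models and the GENMOD outcome model share the same baseline covariates.

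**Secondary models.** MOUD engagement at 7 and 30 days and formal treatment at 30 days reuse the primary analysis (SAP 7.2.5.1 to 7.2.5.3). The negative binomial models for illicit opioid days and overdose (SAP 7.2.5.4 and 7.2.5.7) add the baseline value of the outcome and treatment seeking. The overdose model also adds urine fentanyl.

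**The concern.** The stated analysis set is everyone randomised, with missing outcomes handled by weighting. The covariate rule works against that. It removes people whose outcome was obtained and verified, for a reason that has nothing to do with the outcome. The weights offer no compensation, because they model whether the outcome was observed and not whether the covariates are complete.

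At stake is some precision, agreement between the ITT label and the set actually analysed, and an unplanned choice after database lock if values turn out to be missing.

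**Working it through.** **1. Path of one record through the printed code.** Take a participant with Day 7 engagement verified and sex missing.
- Neither the logistic steps nor GENMOD has a MISSING option on its CLASS statement, and no step fills in covariates.
- By SAS default, a row with a missing predictor gets no predicted value. So `pred07` is missing and the weight 1/`pred07` is missing.
- GENMOD omits a row with a missing weight. It would omit the row anyway, because sex is in the outcome model. Repairing only the weight model would therefore not help.
- The GLIMMIX sensitivity analysis (SAP 7.2.3) uses the same covariates and weight and loses the same row.

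No code is printed for the secondary count models, and their baseline outcome values and urine fentanyl have no row in Exhibit 2. With no rule given, the same default deletion applies.

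**2. Which covariates are exposed.**

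| Covariate | Status |
|---|---|
| Treatment, visit, site, randomisation insurance | Fixed by design or randomisation (SAP 2.2.4.2) |
| Age | Needed for eligibility |
| Race, ethnicity | Unknown level provided |
| Sex | Exposed in the primary model |
| Prior 12-month engagement | Required by the text, but its source is blank in Exhibit 2, a question mark in the variable list, and commented out of the code; exposed once added |
| Treatment seeking, baseline TLFB days, baseline overdose count, urine fentanyl | Exposed in the secondary count models that use them |

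Craving and satisfaction also call for a baseline value, but protocol Table 2 schedules neither at enrolment. That value is absent for everyone. This is a separate problem that a missing-data rule cannot solve.

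**3. The plan's own figure.** Inputs from protocol 12.3: 45% v 53%, two-sided 0.05, 850 per arm, 15% dropout.

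Power = Φ[(δ√n − 1.96·√(2p̄q̄)) / √(p₁q₁ + p₂q₂)], with δ = 0.08, √(2 × 0.49 × 0.51) = 0.7070 and √(0.2475 + 0.2491) = 0.7047.

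At n = 850: (0.08 × 29.155 − 1.3856) / 0.7047 = 1.343, giving 91.0%. The sample size for 90% power is 819 per arm, or 844 with continuity correction, close to the stated 850. Also 850 / 0.85 = 1000 per arm, or 2000 in all. The design reproduces.

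**4. Loss at an assumed missing-covariate rate m.** Evaluable n per arm = 1000 × 0.85 × (1 − m). Outcomes lost = 1700 × m.

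| m (assumed) | n per arm | Observed outcomes lost | Power, 8 points | Power, 7 points |
|---|---|---|---|---|
| 0 | 850 | 0 | 91.0% | 82.4% |
| 1% | 842 | 17 | 90.8% | 82.0% |
| 2% | 833 | 34 | 90.5% | 81.6% |
| 5% | 808 | 85 | 89.6% | 80.4% |
| 10% | 765 | 170 | 88.0% | 78.3% |

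Power for 8 points stays at 90% down to 819 per arm, a loss of 1 − 819/850 = 3.6%.

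**5. Bias.** A simulation followed the SAP's steps with N = 2000 and one binary covariate about 10% missing. It used 150 replicates per mechanism and cluster-robust errors, with an independence working correlation in place of the SAP's exchangeable one. Entries are the mean Day 7 log odds ratio.

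| Missingness | As written | Missing level added | Covariate complete |
|---|---|---|---|
| Completely at random | 0.300 | 0.303 | 0.303 |
| Related to prognosis | 0.311 | 0.313 | 0.309 |
| Related to arm and prognosis together | 0.410 | 0.344 | 0.333 |

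Monte Carlo error is about 0.107/√150 = 0.009. Only the last row shows a shift in the analysis as written. Under completely random missingness, the analysis as written used about 1563 of 1735 observed Day 7 outcomes (standard error 0.104). Adding a missing level used all 1735 (standard error 0.098).

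**The case against.** The primary model is barely exposed. As printed, only sex can remove a row. Prior engagement is undefined and not yet in the code, which is a different defect. Three of the five key secondary outcomes reuse that model. Treatment seeking comes from a chart abstraction with one form per participant (protocol 8.8.2), baseline TLFB and overdose are collected by research staff at enrolment, and urine fentanyl comes from screening. The RCT part of the SAP is described as a first draft, to be finalised in version 4.0. Filling in means would also contradict the no-imputation sentence in protocol 12.6.1. All of this stands, and it sets the size of the point.

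Three stronger inferences are tempting and are not supported:
- *Missing values are to be expected because ancillary Table 8 lists don't know, refused and missing for sex.* That shell belongs to another component. It also has rows for age under 18 and methadone-positive urine, both ineligible, so its rows are generic. How a refusal is stored, as missing or as its own code, is not stated.
- *The secondary models lose much more.* They have more exposed covariates, but the documents give no rate for any of them.
- *The randomised comparison is biased.* That needs missingness related to arm and prognosis jointly. Nothing in the documents suggests this for sex or the other covariates.

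The objection does not remove the core. The Exhibit 2 note is a stated rule and not a silence, and it conflicts with the stated analysis set. Draft status is a reason to settle it before lock.

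**Conclusion.** The point holds in a narrow form. Under the Exhibit 2 note and the printed code, the models are complete-case on covariates, and the weights cannot recover the people removed. With the code as it stands, the primary loss may be close to nil. It grows if prior engagement is added with an incomplete source.

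At assumed losses up to 5%, the cost is about 1.4 points of power for an 8-point difference (91.0% to 89.6%). Power for 7 points falls below the planned 80% only at larger losses (78.3% at 10%). These figures rest on assumed rates and a simple two-proportion test, not on the weighted GEE. This is a cheap improvement and not a threat to the trial's conclusion.

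**What to change.** Replace the Exhibit 2 note with a rule for all models:
- Categorical covariates get a missing/unknown level, merged with another level if sparse. Use it in both weight models, the outcome model and the secondary models.
- Continuous or count baseline covariates take the overall mean plus a missingness indicator.
- Amend protocol 12.6.1 to say that its no-imputation rule concerns outcomes and not baseline covariates. The wording should also allow for SAP 7.2.4.4, which already fills unknown TLFB days in two ways.
- Report by arm any ITT participant with an observed outcome who is still excluded.

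The cost is a revised note, a few lines of code and a one-line protocol clarification. The downside is a few sparse parameters. A near-empty level could be unstable in the weight model, hence the merging rule; the SAP's existing check for weights above 3 also guards against this.

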#### 7.2.5.5 Craving scores

Craving scores at Day 7 will be compared between groups using analysis of covariance (ANCOVA) and will include covariates for outcomes measured at baseline as well as site, age, sex, ethnicity, race, treatment seeking, and insurance status (see **Exhibit 2**). Linear contrasts will be used to estimate treatment differences along with 95% confidence intervals for XR vs. SL.

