| HRQoI                                                           | 6    | RA      |                    | X          | X                   | X                    |
| Crime and Criminal
Justice                                   | 1'   | RA      |                    | X          | X                   | X                    |
| Total Duration in Minutes at Index
Visit                     |      |         | 16                 | 47'        |                     |                      |
| Desire to Use
Scale/Opioid Craving                           | 1'   | RA      |                    |            | X                   |                      |
| Satisfaction Scale
(XR-BUP)                                  | 1'   | RA      |                    |            | X                   |                      |

| Instrument/
Activity                                  | Time | Done by | Study Assessments                                                                                      |                                                                             |                     |                      |
|----------------------------------------------------------|------|---------|--------------------------------------------------------------------------------------------------------|-----------------------------------------------------------------------------|---------------------|----------------------|
|                                                          |      |         | Screening                                                                                              | Enrollment                                                                  | 7-Day
Assessment | 30-Day
Assessment |
|                                                          |      |         | (Index ED Visit 1)                                                                                     |                                                                             | By phone            | By phone             |
| Patient Satisfaction & Adherence (SL-BUP)                | 1'   | RA      |                                                                                                        |                                                                             | X                   |                      |

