#### 8.7.16 Patient Satisfaction & Adherence (SL-BUP)

The Patient Satisfaction & Adherence (SL-BUP) form solicits participant experience with the study medication, and adherence to the study medication, for participants randomized to the SL-BUP arm of the study.

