### 12.6.3.3 Analysis of Secondary Effectiveness Outcomes

Craving and satisfaction assessed at 7 days will be compared between groups using ANCOVA. Counts of self-reported opioid use, health service utilization and overdose events will be compared between groups at both 7 and 30 days using negative binomial regression. All of these

models will include covariates for outcomes measured at baseline as well as site, age, sex, ethnicity/race, treatment seeking and insurance status. Linear contrasts will be used to estimate treatment differences along with 95% confidence intervals in XR vs. SL.

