#### 7.2.5.6 Satisfaction questionnaires

Satisfaction at Day 7 will be compared between groups using ANCOVA and will include covariates for outcomes measured at baseline as well as site, age, sex, ethnicity, race, treatment seeking, and insurance status (see **Exhibit 2**). Linear contrasts will be used to estimate treatment differences along with 95% confidence intervals in XR vs. SL.

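### The craving and satisfaction ANCOVAs call for a baseline-outcome adjustment that the RCT schedule makes impossible; the covariates need to be named for craving and the term removed for satisfaction

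*Combined protocol and SAP*

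**What the plan says.** **The models.** SAP 7.2.5.5 says that the Day 7 craving ANCOVA "will include covariates for outcomes measured at baseline as well as site, age, sex, ethnicity, race, treatment seeking, and insurance status". SAP 7.2.5.6 uses the same formula: "Satisfaction at Day 7 will be compared between groups using ANCOVA and will include covariates for outcomes measured at baseline". Protocol 12.6.3.3 opens with "Craving and satisfaction assessed at 7 days will be compared between groups using ANCOVA", goes on to negative binomial models for opioid use, health service utilization and overdose, and then applies one baseline-covariate sentence to all five outcomes.

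**The measurements.** SAP 7.2.4.5: "Opioid craving scores are measured at Day 7 by a visual analog scale". SAP 7.2.4.6: "Satisfaction is measured at Day 7 on the Patient Satisfaction XR-BUP Questionnaire and the Patient Satisfaction & Adherence SL-BUP Questionnaire". In protocol Table 2 the row "Desire to Use Scale/Opioid Craving" and the two satisfaction rows are marked in the 7-day column and nowhere else. Protocol 8.7.16 describes the sublingual-arm form as one that "form solicits participant experience with the study medication, and adherence to the study medication".

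**The covariate list.** Both SAP sections refer to Exhibit 2. It lists treatment, visit, site, age, sex, ethnicity, race, prior engagement, treatment seeking and insurance. It contains no baseline craving or satisfaction variable and no stand-in for one. Its note reads "Unless noted otherwise, covariate values will be missing if the underlying variable(s) are missing".

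**Status.** Exhibit 5 describes the RCT part of SAP version 3.0 as a first draft. Version 4.0, which has no approval date, is to finalize it before the database is locked.

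**The concern.** Baseline adjustment in an ANCOVA needs a pre-treatment measurement of the outcome. For craving, the RCT does not take one. For satisfaction, none can exist, because the item rates experience with the assigned drug. Two of the secondary effectiveness outcomes in protocol 8.2 (items 5 and 7) thus carry an instruction that nobody can follow, and the analyst must decide what to do instead. The trial is open-label and secondary analyses have no multiplicity adjustment (SAP 9.2), so that decision is better written down in advance.

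For craving there is also a precision question. Severity measures taken at the index visit could do part of the work of the absent baseline, but neither document names them in this model.

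**Working it through.** **Step 1. Is there a baseline value for each outcome covered by the pooled sentence?** Timing is from protocol Table 2.

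| Outcome | Collected at screening or enrollment? | Collected after dosing | Can baseline-outcome adjustment be done? |
|---|---|---|---|
| Opioid-use days (TLFB) | Yes | Day 7, Day 30 | Yes |
| Health service utilization | Yes | Day 7, Day 30 | Yes |
| Overdose | Yes | Day 7, Day 30 | Yes |
| Craving | No | Day 7 | No |
| Satisfaction (either form) | No | Day 7 | No, and not definable before dosing |

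The wording suits three outcomes and fails for two. Craving is measured at baseline in the Ancillary component (protocol Table 4; SAP 7.1.6.6), but those participants are not in the RCT analysis.

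**Step 2. Can the models be fitted?** In a trial fit with 1,700 simulated records and a baseline column left empty throughout, no complete row remained and the fit failed. Without that column all 1,700 rows were used. Omitting the term therefore restores an estimable model.

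**Step 3. Reproduce the stated power.** Inputs, from SAP 10.2 and protocol 12.4.1: 850 per arm, d = 0.16, two-sided 0.05, stated power 90%.

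- Standard error of the standardized difference: √(2/850) = 0.0485.
- Power = Φ(0.16/0.0485 − 1.960) = Φ(1.338) = 0.910.
- Detectable d at exactly 90% power: (1.960 + 1.282) × 0.0485 = 0.157, which rounds to 0.16.

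The stated figure reproduces with no covariate at all, so removing the baseline term leaves it at 0.910.

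**Step 4. What could named baseline covariates add for craving?** Let R be the correlation of the added covariates with Day 7 craving, beyond the covariates already in the model. The residual SD becomes √(1 − R²), and power = Φ(0.16/[0.0485 × √(1 − R²)] − 1.960). The documents give no value for R, so it is an assumption, shown over a range.

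| Assumed R | Power at d = 0.16 | Detectable d at 90% power |
|---|---|---|
| 0 | 0.910 | 0.157 |
| 0.2 | 0.920 | 0.154 |
| 0.3 | 0.933 | 0.150 |
| 0.4 | 0.949 | 0.144 |
| 0.5 | 0.968 | 0.136 |

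**Step 5. Do suitable covariates exist?** Table 2 has COWS at screening and TLFB at enrollment. SAP 5.2 already summarizes baseline COWS and opioid-use days in the week before randomization.

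**The case against.** The strongest reply is that the phrase can be read as applying only to outcomes that do have a baseline measurement. Protocol 12.6.3.3 is a single sentence over a mixed group of outcomes, and the SAP appears to have carried its wording into each subsection. On that reading craving and satisfaction have no baseline-outcome term and there is nothing to fail. The reading is possible, but neither document states it. The SAP elsewhere tailors covariates by outcome: fentanyl in the urine screen is added for overdose alone. A reader cannot be sure that the exception is implied.

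Three stronger readings are tempting and are not supported:

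- **That the models cannot be run, or that every record is lost.** A reader might infer this from the Exhibit 2 note. The note concerns missing values of covariates, and the exhibit lists no baseline-outcome variable for any model, not even for opioid-use days, where a baseline exists. It does not tell anyone to build an empty column. The failed fit in step 2 shows only what would happen if someone did.
- **That the term will be swapped out after the results are seen.** Whether a baseline exists is settled by the visit schedule, not by the data, and SAP 4.0 is a planned opportunity to correct the text before lock.
- **That collected severity data are ignored and the comparison is biased.** Baseline opioid use and overdose enter their own models, and SAP 7.2.6 plans exploratory work on patient characteristics. Under randomization, leaving a prognostic covariate out does not bias the treatment difference.

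It is also fair to say that the documents offer no evidence on how well TLFB days or COWS predict Day 7 craving, so the gain could be close to nil.

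**Conclusion.** The point holds as a defect of specification. For craving and satisfaction, the adjustment in SAP 7.2.5.5 and 7.2.5.6, and in the pooled sentence of protocol 12.6.3.3, cannot be carried out, and no replacement is named. Its weight is low. Both models are estimable without the term, power stays at 0.910 against a stated 90%, no bias follows, and neither outcome is among the five key secondary outcomes in SAP 7.2.4. The primary analysis is not touched.

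The forgone precision concerns craving only. Over an assumed R of 0 to 0.5, power at d = 0.16 would run from 0.910 to 0.968. That range rests on the assumed correlation, 850 evaluable participants per arm and a normal approximation. The statement on bias rests on randomization and concerns the covariate choice alone; missing Day 7 scores are a separate question.

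**What to change.** Before RCT database lock, in SAP version 4.0:

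- **7.2.5.5 (craving):** replace the baseline-outcome term with baseline TLFB opioid-use days and baseline COWS, and add both to Exhibit 2, marked for this model.
- **7.2.5.6 (satisfaction):** delete the baseline-outcome term and keep the other covariates.
- **Protocol 12.6.3.3:** make the exception for craving and satisfaction only. A blanket replacement of the phrase would strip valid baseline adjustment from opioid use, health service utilization and overdose.

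The cost is wording in three places and two rows in Exhibit 2, with no new data and no change to the sample size. Two extra degrees of freedom are negligible against 1,700 evaluable participants (2 × 850). One consequence should be accepted knowingly: the Exhibit 2 note would then apply to the new covariates, so a participant without an enrollment TLFB would drop out of the craving model unless a rule is given. COWS is needed to establish eligibility and should be close to complete.
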